#### 6‐minute walk test

2.4.1

The 6‐minute walk test (6MWT) distance is an objective and well‐validated measure of walking ability that predicts mobility loss and mortality in PAD with excellent test‐retest reliability, and is our primary endpoint.^12^, ^34^, ^35^ Distances walked between repeat 6MWTs by PAD patients have a high‐reliability coefficient (>0.90) and a low coefficient of variation (~10%).^34^, ^35^ The 6MWT offers several advantages over treadmill testing in PAD as it correlates more closely with physical activity levels in the community and is not associated with a learning effect when repeated testing is performed.^36^, ^37^ Participants perform a 6MWT by walking back and forth along a 100‐ft hallway using a standard protocol.^19^ The total distance walked, claudication onset time, defined as the time at which ambulation could not continue due to maximal pain, and the pain‐free walking distance, are recorded to quantify the severity of claudication. In a recent randomized study, the minimal clinically important difference (MCID) for 6MWT distance for small, moderate and large changes after 3 months of home‐exercise were 11, 28, and 45 m, respectively.^38^

#### Survey data

2.4.2

Data from both the Walking Impairment Questionnaire (WIQ) and Short‐Form 36 (SF‐36) are collected as secondary outcomes. All surveys are self‐administered by the participant. The WIQ is a validated PAD‐specific measure of patient‐reported walking ability including walking speed and distance, and the ability to climb stairs.^39^ Each domain is scored on a scale of 0 to 100 with 0 representing the most significant limitation and 100 representing no difficulty. Changes in walking ability as a result of therapeutic interventions, such as exercise, have been correlated with improvements in the WIQ score.^18^, ^19^ The SF‐36 is a well‐validated QoL assessment that is frequently used to assess changes in response to therapeutic interventions in PAD, including trials of home exercise.^19^, ^40^ The SF‐36 includes eight health dimensions (eg, physical functioning, bodily pain, general health) which will be converted to a scale ranging from 0 (worst possible score) to 100 (best possible score).^40^

#### Daily ambulatory activity

2.4.3

Daily ambulatory activity is assessed as a secondary endpoint using a wrist‐worn activity monitor (Fitbit Charge HR) which measures step counts, actigraphy, and resting HR. Fitbit devices have been shown to be more valid than other consumer activity monitors in measuring walking activity.^41^ Participants are instructed to wear the device daily during waking hours and remove it at night to recharge. The device is connected via Bluetooth to their personal smartphone device via the Fitbit app. The device records the number of steps taken and other data points on a minute‐to‐minute basis. With participants' consent, a member of the study team remotely accesses the participants' activity data using the Fitbit online dashboard.

#### Ankle‐brachial index

2.4.4

All participants undergo measurement of the ABI at baseline to determine eligibility. The ABI is associated with the degree of functional impairment and the rate of functional decline among older adults in PAD.^28^ Since prior randomized trials of exercise therapy in PAD have not demonstrated an improvement in ABI after exercise, the ABI is not repeated after the 6MWT or during any follow‐up visit. After 10 minutes at rest, an ABI is obtained from the more severely diseased lower extremity using a standard protocol.^42^ Both the ankle and brachial systolic pressures are measured by Doppler. Measurements are taken from the posterior tibial and dorsalis pedis arteries at the ankle in both legs, and the higher of the arterial pressures from the more severely diseased legs is recorded as the resting ankle systolic pressure. Similarly, the higher systolic pressure is recorded as the brachial systolic pressure for the ABI, calculated as the ratio of the ankle systolic pressure to the brachial systolic pressure.

### Statistical methods

2.5

#### Key endpoints

2.5.1

Our primary outcome is change in 6MWT distance from baseline to 12 weeks (ie, end of program completion). All remaining outcomes are secondary and include survey data from the WIQ and SF‐36 questionnaires, changes in daily ambulatory activity from the Fitbit, modifiable PAD risk factors (such as blood pressure and smoking status), self‐reported exercise and medication adherence collected via the smartphone app, the degree of participant engagement with the app individual features (eg, chats, educational videos), and pre‐specified clinical endpoints (eg, emergency department visits, hospital admissions, critical limb ischemia, cardiovascular events, or death prior to program completion).

#### Power and sample size calculations

2.5.2

We powered the study on the primary outcome of 6MWT distance. All other outcomes are secondary. In a recent study of HBET, the estimated effect size (ES) was a Cohen's d = 0.96 in the comparison of change in 6MWT distance between HBET and an attention control condition based on a sample size of 50 per group (mean change of 55 ± 57 m in the intervention group vs no change in the control group).^38^ Assuming an alpha of 0.05, 50 participants total (25 per group) provides 93% power to detect a similar effect. If we have a 32% dropout rate,^15^, ^19^, ^43^ the power decreases to 80%. If all 50 participants are retained, however, the minimum detectable difference between groups at 80% power is 45 m (SD 57 m). For reference, these are considered large effect sizes.^38^ Nonetheless, such differences have been seen in the literature and are considered justified.

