### Hypotheses and objectives

1.2

The overarching goal of the Smart Step Study is to evaluate the feasibility of a smartphone‐enabled, home‐based exercise program for PAD in a low‐resource setting where access to a traditional, facility‐based SET program is essentially absent. The primary outcome of interest is functional improvement after 12‐weeks of enrollment. We will also assess for participant engagement with the smartphone app and phone‐based coaching. If successful, this study will generate novel information on how PAD patients in economically disadvantaged settings respond to a smartphone‐based exercise program and provide evidence to proceed with larger trials to determine efficacy.

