#### Statistical analysis

2.5.3

For analyses involving comparisons of groups we will perform two‐sample, independent *t*‐tests for normally distributed data, and logarithmic transformations for positive skewed distributions. For highly skewed data where log transformation does not adequately correct the skew, we will use non‐parametric rank‐order tests such as the Wilcoxon rank sum. For between‐group differences, 95% confidence intervals will be constructed, and multivariable adjustments using linear regression will be used where large group imbalances exist. Analyses will be performed as intention‐to‐treat, but we will also do sub‐group analyses based on the degree of engagement with the program. Multiple imputations will be used for missing data using established methods,^44^ and per‐protocol analyses will also be conducted. The a priori level for statistical significance was a two‐sided *P* < .05.

There are no sub‐studies planned, but we will perform predefined subgroup analyses to explore efficacy according to several baseline characteristics including age, ABI results, functional status, revascularization history, and degree of engagement with the smartphone app and coaching program.

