In contrast, the more recent HONOR Trial by McDermott et al of an HBET intervention using a waist‐worn pedometer (Fitbit Zip) yielded substantially different results. In HONOR, 200 patients with symptomatic PAD were randomized to HBET or to usual care with walking advice only.^19^ Participants in the home‐exercise group completed 12‐weeks of exercise, initially with weekly sessions at the hospital for 4 weeks followed by 8 weeks of completely home‐based exercise with telephone coaching and with the wearable monitor. After 9 months of follow‐up, there was no significant difference in 6‐minute walk distance between the home‐based intervention and usual care group with a surprising trend towards better performance among participants in the usual care group who did not receive exercise coaching (5.5 vs 14.4 m; 95% CI, −26.0 to 8.2; *P* = .31). Total step counts from the Fitbit's accelerometer did not statistically differ between the two groups.

The Smart Step Study offers several important additions to these and other prior HBET studies. First, whereas prior studies have used passive activity trackers such as pedometers and actigraphs only, the use of a smartphone app to enable self‐management and provide clinical support is a novel addition which has only been recently explored in PAD management,^23^, ^45^ and to our knowledge has not been previously deployed in a low‐resource hospital setting. The addition of Movn and INTERVENT also offer novel additions in smartphone‐based delivery and coach training. The study coach underwent rigorous coach training by INTERVENT which has extensive experience in behaviorally‐oriented telephonic health coaching in patients with ischemic heart disease and stroke.^47^

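### The stated 93% power, 80% power after dropout and 45 m detectable difference fit a normal approximation; the planned t-test gives about 91–92%, 78% and 46 m

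*Protocol article*

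**What the plan says.** Section 2.5.2 (Power and sample size calculations) of the protocol article takes its planning effect from one earlier home-exercise study: "the estimated effect size (ES) was a Cohen's d = 0.96 in the comparison of change in 6MWT distance". That is a gain of 55 m (SD 57 m) against no change in controls. It then states that, at an alpha of 0.05, "50 participants total (25 per group) provides 93% power to detect a similar effect". With 32% dropout, "the power decreases to 80" per cent. With all 50 retained, "the minimum detectable difference between groups at 80% power" is given as 45 m with SD 57 m. The section adds openly that these are large effects.

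Section 2.5.3 (Statistical analysis) names the test: a two-sample independent t-test for normally distributed data, with log transformation or a rank test for skewed data. On the significance level it says: "The a priori level for statistical significance was a two‐sided" P < .05. Regression adjustment is foreseen only where large imbalances between groups appear. No formula or software is given for the power figures.

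**The concern.** A power statement should describe the test that will be run. With 48 degrees of freedom at full retention and 32 after dropout, the t critical value exceeds 1.96 by enough to move the second digit of the power. All three figures shift in the direction that flatters the design. The largest shift falls on the 80% after dropout, the conventional floor, which the plan presents as still met after heavy attrition. What is at stake is the accuracy of the power statement, not whether the trial can be run as designed.

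**Working it through.** **Inputs** (sections 2.5.2 and 2.5.3, with 1:1 allocation from section 2.1)
- Two-sided alpha 0.05; d = 0.96, or unrounded 55/57 = 0.965; SD of change 57 m.
- n = 25 per arm. With 32% dropout, 50 × 0.68 = 34 completers, so n = 17 per arm.

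**Step 1: reproduce the stated figures (normal approximation)**

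Power = Φ(d·√(n/2) − 1.960).
- n = 25: d·√12.5 = 3.394 (d = 0.96) or 3.411 (55/57), so power is Φ(1.434) = 92.4% or Φ(1.452) = 92.7%. Stated: 93%.
- n = 17: d·√8.5 = 2.799 or 2.813, so power is Φ(0.839) = 79.9% or Φ(0.853) = 80.3%. Stated: 80%.
- Detectable difference = (1.960 + 0.842) × 57 × √(2/25) = 45.2 m. Stated: 45 m.

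All three match. A one-sided t-test does not fit (95.6% and 86.3% at d = 0.96). Use of the normal approximation is inferred from this match.

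**Step 2: the planned test**

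Under the two-sided t-test, the statistic follows a noncentral t distribution with df = 2n − 2 and noncentrality d·√(n/2).

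| | Stated | Normal approximation | t-test | Stated minus t-test |
|---|---|---|---|---|
| Power, 25 per arm (df 48, critical value 2.011) | 93% | 92.4–92.7% | 91.4–91.7% | 1.3–1.6 points |
| Power, 17 per arm (df 32, critical value 2.037) | 80% | 79.9–80.3% | 77.5–77.9% | 2.1–2.5 points |
| Detectable difference, 25 per arm, 80% power | 45 m | 45.2 m | 46.1 m | about −1 m |

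At 17 per arm the t-test's detectable difference is 56.5 m, just above the 55 m planning effect. This is the same shortfall expressed in metres. With 18 completers per arm the t-test gives 79.9–80.3%.

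**Step 3: would baseline adjustment recover the figures?**

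Table 3 gives a baseline SD of 113 m in the first 15 patients. Assume the same SD at 12 weeks and a change SD of 57 m:
- 57² = 2 × 113² × (1 − ρ), so ρ = 1 − 3249/25538 = 0.873.
- ANCOVA residual SD = 57 × √((1 + ρ)/2) = 57 × √0.936 = 55.2 m.
- With d = 55/55.2 and one degree of freedom fewer, power is 93.2% (25 per arm) and 80.4% (17 per arm), and the detectable difference at 25 per arm is 44.6 m.

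The correlation is uncertain, so here is a range with the change SD held at 57 m:

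| ρ | Power, 25 per arm | Power, 17 per arm | Detectable difference, 25 per arm |
|---|---|---|---|
| 0.80 | 94.1% | 81.9% | 43.8 m |
| 0.87 | 93.2% | 80.4% | 44.6 m |
| 0.90 | 92.9% | 79.8% | 44.9 m |
| 0.95 | 92.3% | 78.8% | 45.5 m |

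Across this range ANCOVA does better than the unadjusted t-test on change.

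**Step 4: a smaller effect**

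Section 2.4.1 cites 28 m as a moderate difference. With SD 57 m, d = 28/57 = 0.491, and t-test power is 39.8% at 25 per arm and 28.5% at 17 per arm.

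**The case against.** The strongest reply is that nothing here is wrong in a way that matters. The figures follow from a standard textbook formula. The gaps are 1 to 2.5 points and 1 m, far smaller than the uncertainty in a d of 0.96 taken from one study. The only gap above 2 points concerns a hypothetical dropout rate, and one more completer per arm closes it. Most of this stands: it limits the point to a minor correction. It does not remove it, because the article names a t-test and the stated 80% is not what that test gives.

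A reader might also infer more than the documents support:
- **That the pilot succeeds or fails on P < .05.** Section 1.2 makes feasibility the overarching goal, names 6MWT change as the primary outcome and also assesses engagement. It says only that a successful study would "provide evidence to proceed with larger trials to determine efficacy". No rule ties success to a P value.
- **That the trial is underpowered for its own target of 28 m.** That figure is quoted from a cited study and is not adopted as a target. Low power at 28 m follows from a 45 m detectable difference, which the article discloses and calls large.
- **That a control gain of 14.4 m would sharply cut the power.** The Discussion reports that gain at 9 months from a trial with a "trend towards better performance among participants in the usual care group who did not receive exercise coaching", in which the home-exercise arm gained 5.5 m. Pairing that control arm with the 55 m gain of a different study is not a scenario the documents support.
- **That progression thresholds are missing.** A condensed article may leave these to the full protocol.

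Against the ANCOVA remedy, it is fair to say that ρ = 0.87 mixes a baseline SD from 15 interim patients with a change SD from another study. It is illustrative only.

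**Conclusion.** The point holds as a small correction. For the test the plan names, power is about 91–92% rather than 93% at full retention and about 78% rather than 80% after 32% dropout, and the detectable difference is 46 m rather than 45 m. These results take the plan's own inputs as given (55 m, SD 57 m, 17 completers per arm after dropout) and assume that the t-test branch of the analysis applies. The design remains workable and the sample size need not change. That ANCOVA would restore the stated figures depends on a correlation near 0.87 and equal SDs at both visits.

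**What to change.** Do one of the following.

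1. Restate section 2.5.2 as about 91–92% power at 25 per arm, about 78% at 17 per arm and a 46 m detectable difference, naming the two-sided two-sample t-test as the basis. The cost is slightly less favourable figures.
2. In section 2.5.3, make the primary analysis an ANCOVA of 12-week 6MWT distance on baseline 6MWT distance for all participants, prespecified rather than used only when large imbalances appear. Quote about 93%, 80% and 45 m with the assumed correlation and its sources. Baseline 6MWT is already collected, so the cost is a change of wording, best made before the outcome data are compared by arm.

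Optionally, add a sentence that a non-significant result would not exclude a 28 m benefit, for which t-test power is about 40% at full retention and 28% after 32% dropout. The 95% confidence intervals already planned would carry that message. No additional patients or measurements are needed.

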#### Statistical analysis

2.5.3

For analyses involving comparisons of groups we will perform two‐sample, independent *t*‐tests for normally distributed data, and logarithmic transformations for positive skewed distributions. For highly skewed data where log transformation does not adequately correct the skew, we will use non‐parametric rank‐order tests such as the Wilcoxon rank sum. For between‐group differences, 95% confidence intervals will be constructed, and multivariable adjustments using linear regression will be used where large group imbalances exist. Analyses will be performed as intention‐to‐treat, but we will also do sub‐group analyses based on the degree of engagement with the program. Multiple imputations will be used for missing data using established methods,^44^ and per‐protocol analyses will also be conducted. The a priori level for statistical significance was a two‐sided *P* < .05.

There are no sub‐studies planned, but we will perform predefined subgroup analyses to explore efficacy according to several baseline characteristics including age, ABI results, functional status, revascularization history, and degree of engagement with the smartphone app and coaching program.

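### The log-transformation rule in section 2.5.3 does not exempt change scores, so it cannot be carried out as written on the primary outcome if the 6MWT change is judged positively skewed

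*Protocol article*

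**What the plan says.** Key endpoints (2.5.1) defines the analysed variable: "Our primary outcome is change in 6MWT distance from baseline to 12 weeks". Study measures (2.4) also words the disease-burden and quality-of-life scores and the Fitbit activity outcome as changes.

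Statistical analysis (2.5.3) opens its rule with "For analyses involving comparisons of groups we will perform" and lists three steps:

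1. Two-sample t-tests for normally distributed data.
2. "logarithmic transformations for positive skewed distributions".
3. "For highly skewed data where log transformation does not adequately correct the skew", a non-parametric test such as the Wilcoxon rank sum.

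The section exempts no outcome, names no offset, and does not say that distances rather than changes are logged. It gives no criterion for calling data skewed or highly skewed. It also commits to intention-to-treat analysis, multiple imputation and 95% confidence intervals for between-group differences.

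Power and sample size calculations (2.5.2) plans on a "mean change of 55 ± 57 m in the intervention group vs no change in the control group".

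**The concern.** The logarithm exists only for positive numbers. A 12-week change in walking distance is negative for anyone who walks less far than at baseline, and section 2.5.2 puts the control mean at zero. Non-positive changes are therefore built into the plan's own assumptions and are not rare exceptions.

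If the observed changes look positively skewed, the printed rule sends the analyst to a step that cannot be done on the variable as defined. Three ways round it are open: add a constant, leave out those who did not improve, or log the distances and compare ratios. Each answers a different question and none is specified. The rank fallback does not clearly cover the case. Its trigger is a log that was taken and did not correct high skew, so it does not address moderate skew or values with no logarithm.

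At stake is the prespecification of the one powered comparison. Its test and scale would depend on a look at the outcome in a trial where, by section 2.4, blinding was not considered feasible. The power calculation and the MCIDs of 11, 28 and 45 m in section 2.4.1 are all in metres of change.

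**Working it through.** **Inputs from section 2.5.2.** Mean change is 55 m (HBET) and 0 m (control), with SD 57 m. The stated d is 0.96, and 55/57 = 0.965, which implies the same SD in both arms. There are 25 per arm and alpha is 0.05, two-sided by section 2.5.3.

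**The plan's own figures first** (normal approximation):
- Power, 25 per arm: Φ(0.96 × √(25/2) − 1.960) = Φ(3.394 − 1.960) = 92.4%. With d = 55/57 it is 92.7%. Stated: 93%.
- Power, 17 per arm (32% dropout): Φ(0.96 × √(17/2) − 1.960) = Φ(2.799 − 1.960) = 79.9%. Stated: 80%.
- Minimum detectable difference: 57 × (1.960 + 0.842) × √(2/25) = 45.2 m. Stated: 45 m.

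These reproduce and are not in dispute. The noncentral t gives slightly less favourable values: 91.4%, 77.5% and 46.1 m.

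**Share with no defined logarithm**, P(change ≤ 0) = Φ(−mean/SD), normality assumed:
- Control: Φ(0) = 50.0%, or 12.5 of 25. This holds for any continuous symmetric distribution centred on zero, whatever the SD.
- HBET: Φ(−55/57) = 16.7%, or 4.2 of 25.
- Total: 12.5 + 4.2 = 16.7 of 50.

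| Assumption | Total at or below 0, of 50 |
|---|---|
| SD 40 m, effect 55 m | 14.6 |
| SD 57 m, effect 55 m | 16.7 |
| SD 75 m, effect 55 m | 18.3 |
| SD 57 m, effect 45 m | 17.9 |
| SD 57 m, effect 28 m | 20.3 |
| SD 57 m, effect 11 m | 23.1 |

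**The same count under skew**, since skew is what triggers the log step. Assume a shifted gamma with shape 4 (skewness 1), same means and SD, so that change = mean + 57 × (G − 4)/2. For shape 4, P(G ≤ x) = 1 − e^(−x)(1 + x + x²/2 + x³/6).
- Control: x = 4, giving 1 − 0.0183 × 23.667 = 56.7%, or 14.2 of 25.
- HBET: x = 4 − 2 × 55/57 = 2.070, giving 15.6%, or 3.9 of 25.
- Total: about 18 of 50, so the count does not depend on normality.

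**How far the choice of workaround matters.** Simulated power, 5,000 runs, 25 per arm, planning effect:

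| Analysis | Normal changes | Right-skewed changes (skewness 1) |
|---|---|---|
| t-test on raw change | 92% | 92% |
| Wilcoxon | 90% | 94% |
| Log, minimum shifted to 1 m | 77% | 97% |
| Log, minimum shifted to 50 m | 90% | 97% |
| Log, non-positive changes dropped | 37% | 16% |

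**Illustration only: dropping non-positive changes.** Under normality the mean among positive changes is 57 × 0.798 = 45.5 m in controls and 55 + 57 × 0.2505/0.8327 = 72.1 m in HBET. The 55 m difference becomes 72.1 − 45.5, about 27 m. The plan does not prescribe this deletion.

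**The case against.** The strongest reply is that the log step may never be reached. If the changes look normal, section 2.5.3 sends them to the t-test, and nothing in the article shows that 12-week 6MWT change is positively skewed. This stands and makes the problem conditional.

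A reader might infer that the plan would discard participants who did not improve, halving the effect from 55 to 27 m or cutting power to 37%. The document does not support that. It prescribes no such deletion, and its intention-to-treat commitment contradicts one. The 27 m figure also assumes normal data, which the rule assigns to the t-test, and is a difference of raw truncated means, not the result of a log analysis.

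A reader might also infer that no log analysis is possible without losing people. Walking distances are positive in practice (baseline mean 363.5 m, SD 113.0, Table 3), and log ratios of distances would keep everyone with a positive distance. That is true, but the estimate is then a ratio, not metres, and the plan does not state it.

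Nor does the rank fallback rule out a result in metres: a Hodges-Lehmann shift with a 95% CI is in metres, although it is not the mean difference and the plan does not mention it. How to pool a rank test over imputations is an implementation detail and is not counted here.

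Finally, a generic log-then-rank sequence is conventional for non-negative outcomes such as app use, and this is a condensed article on a pilot trial whose analysis plan is not shown. Both points lower the severity. They do not make the printed rule workable for a change score.

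**Conclusion.** The point holds in a conditional form. As printed, the rule covers the primary outcome and cannot be carried out on it whenever the change is judged positively skewed, unless the analyst makes a choice that the plan leaves open. From the planning values about 17 of 50 participants would have no defined logarithm (14.6 to 23.1 over the SDs and effects tried, about 18 under the skewed example). About three times as many of them are controls as HBET participants (12.5 against 4.2). This rests on equal SDs, full retention of 50 and, for the 16.7, normality.

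The consequence is loss of prespecification of the primary test and scale, not a demonstrated bias or loss of power. With normal changes, shifted-log power ran from 77% to 90% with the constant alone. In the skewed example the shifted log did well, at 97%. The sample-size figures are sound. Severity: should-fix.

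**What to change.** In section 2.5.3:

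1. State that change scores are not log-transformed. This covers the primary outcome and the WIQ, SF-36 and Fitbit changes.
2. Name one primary analysis in advance: the between-arm difference in 12-week 6MWT distance, in metres, from a linear model adjusted for baseline 6MWT, with a 95% CI, whatever the observed shape.
3. Keep a rank test as a sensitivity analysis. If an interval is wanted with it, specify the Hodges-Lehmann shift.
4. Keep the log step only for strictly positive level outcomes such as average daily steps.

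Item 1, with any single fixed test in metres, cures the defect. Baseline adjustment in item 2 goes further: it usually improves precision and replaces, for this covariate, the present rule of adjusting only where large imbalances appear.

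The cost is wording. Baseline 6MWT is already collected (Table 2), and no new data or change in sample size is needed. The Results section shows that participants were already completing follow-up, so the change should be dated and made before outcomes are compared by arm.

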### Trial design and oversight

2.1

The Smart Step Study (ClinicalTrials.gov NCT03479255) is a single‐site, prospective, open‐label, pilot randomized trial of patients with symptomatic PAD who are eligible for SET. The study design is illustrated in Figure 1. Eligible subjects are randomized to either a smartphone‐enabled HBET program or to walking advice with standard exercise guidance. Potential participants are recruited from the vascular surgery and cardiology clinics at Grady Memorial Hospital, a tertiary academic medical center and public benefit hospital in downtown Atlanta, GA, and screened for eligibility. Eligible participants are then randomized in a 1:1 ratio using a random number generator. Women are oversampled to achieve a 50% target representation. The study protocol has been approved by the Institutional Review Board at Emory University and the Research Oversight Committee at Grady Memorial Hospital.

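### Baseline 6MWT distance enters the primary comparison only if a large imbalance is seen; it should be a fixed covariate, though the gain in precision is modest

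*Protocol article*

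**What the plan says.** The Key endpoints section states: "Our primary outcome is change in 6MWT distance from baseline to 12 weeks". The Power and sample size calculations section sizes the trial on an unadjusted two-group comparison of that change. It takes from an earlier trial a "Cohen's d = 0.96 in the comparison of change in 6MWT distance between HBET and an attention control condition", that is, a "mean change of 55 ± 57 m in the intervention group vs no change in the control group".

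The Statistical analysis section then plans two-sample independent t-"tests for normally distributed data, and logarithmic transformations for positive skewed distributions", with a rank test if the skew persists. Regression appears only as a conditional step: "multivariable adjustments using linear regression will be used where large group imbalances exist". Baseline 6MWT distance is not named as a covariate, although Table 2 shows that it is measured in everyone at entry.

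**The concern.** The 6-minute walk test section itself reports high repeat-test reliability for this measure. Baseline distance can therefore be expected to predict 12-week distance strongly before any patient is randomised. A covariate of that kind belongs in the model because it is prognostic. The stated rule instead makes adjustment depend on how the randomisation happened to fall.

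Two things follow. First, subtracting the baseline does not fully remove a chance baseline difference. When the correlation is below 1, participants who start low tend to gain more than those who start high, so part of the imbalance passes into the contrast of changes. Second, the change score treats the baseline slope as exactly 1 instead of estimating it, which costs some precision. With about 25 per arm, chance imbalances are not rare, and either effect can be avoided at almost no cost.

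**Working it through.** **Inputs**
- From Power and sample size calculations: SD of change 57 m, d = 0.96 (55/57 = 0.965), 25 per group. With 32% dropout, 34 remain, or 17 per group.
- From Statistical analysis: two-sided alpha 0.05.
- From Table 3: baseline 6MWT SD 113.0 m, in the first 15 participants.
- Assumed: the 12-week SD equals the baseline SD. The article does not give the baseline-to-12-week correlation r, so a range of 0.5 to 0.95 is shown.

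**1. The plan's own figures.** The article says that "50 participants total (25 per group) provides 93% power to detect a similar effect". By the normal formula, power = Φ(d·√(n/2) − 1.96):
- 25 per group: 92.4% with d = 0.96, 92.7% with 55/57.
- 17 per group: 79.9% and 80.3%.
- Detectable difference at 80% power: (1.960 + 0.842) × 57 × √(2/25) = 45.2 m.

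The stated 93%, 80% and 45 m reproduce. By the noncentral t with d = 0.96, the values are 91.4%, 77.5% and 46.1 m. The t values are the fair comparator for a regression model and are used below.

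**2. Implied correlation.** With equal SDs, Var(change) = 2·SD²·(1 − r), so r = 1 − 57²/(2 × 113²) = 1 − 3249/25538 = 0.873.

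**3. Residual variance after adjustment.** Ratio to the change-score variance = (1 + r)/2 = 0.936, a cut of 6.4%. Residual SD = 57 × √0.936 = 55.2 m.

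**4. Detectable difference after adjustment.** Estimating the slope costs one degree of freedom (47 instead of 48). It also inflates the variance, on average, by 1 + 1/(2n − 4) = 1 + 1/46 = 1.022.
- SE unadjusted: 57 × √(2/25) = 16.1 m.
- SE adjusted: 55.2 × √(0.08 × 1.022) = 15.8 m.

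| r (assumed) | Variance cut | Detectable difference, 25/arm | Power at d = 0.96, 25/arm | Power, 17/arm |
|---|---|---|---|---|
| unadjusted | – | 46.1 m | 91.4% | 77.5% |
| 0.5 | 25% | 40.4 m | 96.7% | 86.9% |
| 0.7 | 15% | 43.0 m | 94.6% | 82.5% |
| 0.873 | 6.4% | 45.1 m | 92.5% | 78.7% |
| 0.9 | 5% | 45.4 m | 92.1% | 78.1% |
| 0.95 | 2.5% | 46.0 m | 91.5% | 77.1% |

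The table holds the change SD at 57 m. On that footing r = 0.5 would imply a baseline SD of 57/√(2 × 0.5) = 57 m, far from the observed 113 m, so the upper rows are the less likely ones.

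In participants at r = 0.873: 50/0.936 = 53.4, or 53.4/1.022 = 52.3 after the slope cost. The gain is thus worth about 2 to 3.

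**5. Imbalance left in the change score.** SE of the baseline difference = 113 × √(2/25) = 32.0 m. The part carried into the contrast is (1 − r) = 0.127 of it: 0.127 × 32.0 = 4.1 m for one SE, 8.1 m for two. Against the contrast's SE, 4.1/16.1 is about a quarter.

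**6. How often imbalance arises.** A baseline difference above 0.5 SD occurs by chance with probability 2 × [1 − Φ(0.5/√0.08)] = 8%, and above 0.2 SD with probability 48%. Whether the comparison is adjusted would thus vary widely with where a threshold was set.

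**The case against.** The strongest reply is that nothing here is invalid. Allocation is random ("Eligible participants are then randomized in a 1:1 ratio using a random number generator"), so the t-test on change is unbiased for the treatment effect over repeated randomisations. The change score already removes most of the baseline variance. This stands, and it limits the point to precision and to the handling of chance imbalance in the one trial that is run.

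A reader might infer that the rule biases the result or inflates the false-positive rate. The documents do not support that. Imbalance can be judged on baseline data without sight of outcomes. In simulation at r from 0.5 to 0.95, a fixed threshold of 0.2 or 0.5 SD on baseline 6MWT kept type I error at 0.038 to 0.050. It rose to about 0.057 to 0.073 only when the better of the two analyses could be chosen, and the article grants no such choice. Nor does it say that the adjusted result would replace the t-test; it can be read as supplementary.

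The meaning of a large imbalance, the covariate list and the status of the adjusted estimate may stand in an analysis plan that is not shown. Their absence from a condensed article is not held against it. What remains open to comment is the stated rule that adjustment is conditional on imbalance.

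It is also fair to say that this is a pilot with a feasibility goal, sized for differences of 45 to 55 m. A shift of 4 to 8 m should not be dramatised by setting it beside the 11 m small MCID, which neither analysis could resolve.

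**Conclusion.** The point holds as a modest improvement to a stated rule. Adjustment for baseline 6MWT distance should not depend on observed imbalance. On the article's own SDs, fixed adjustment gains 6.4% of variance, about 1 m in the detectable difference and about 1 percentage point of power. It also removes a shift of about 4 m per SE of baseline difference.

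A reader might take this as a material loss of power. It is not one at r near 0.87, and at r = 0.95 there is practically no gain: 46.0 against 46.1 m with 25 per arm, and a fraction of a point lower power with 17. The case rests on fixing a prognostic covariate in advance at almost no cost, not on sample size.

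The size depends on r, which is derived from an SD in 15 participants, a change SD from another trial and an assumption of equal SDs. The sample size need not change.

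**What to change.** In the Statistical analysis section, state that the primary analysis is a linear regression of 12-week 6MWT distance (or its change from baseline) on arm and baseline 6MWT distance, in all randomised participants and whatever the observed balance. With baseline in the model, the two forms of outcome give the same treatment estimate. Delete the imbalance trigger for the primary outcome and keep the unadjusted t-test as a sensitivity analysis. Adjust the WIQ and SF-36 comparisons for their own baseline values, which Table 2 shows are already collected.

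The cost is one sentence and one degree of freedom, with no new data.
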